## Abstract

**Background:**

Research has indicated that depression prevention programs attenuate the development of symptoms of depression in adolescents. To implement these programs on a large scale, implementation in a school setting with teachers providing the programs is needed. In the present study, the effectiveness of the Dutch depression prevention program Op Volle Kracht (OVK) provided by school teachers during school hours with adolescents from high risk neighborhoods will be tested. The mediating effects of cognitive distortions and alexithymia will be evaluated as well. We hypothesize that the OVK program will prevent or decrease reported depressive symptoms, and that this association will be mediated by cognitive distortions and alexithymia.

**Methods/Design:**

Schools with at least 30% of their pupils living in low income areas in the Netherlands are invited to participate in the study. Classes from vocational training up to pre-university level are eligible and 1324 adolescents (11-14 years) will be participating in the study. Randomisation will be done at class level, randomly assigning participants to an intervention group (OVK) and a control group (care as usual), stratifying by school level (high versus low). Trained school teachers will be delivering the program, which covers cognitive-behavioral and social problem-solving skills. Longitudinal data will be collected with self-report measurements administered in the school setting at baseline, post intervention and at two follow ups (at 6 and 12 months). Primary outcome is the level of depressive symptoms, and secondary outcomes include: cognitive errors, response style, attributional style, alexithymia, stressful life events, substance use, happiness, and school grades.

**Discussion:**

If the OVK program proves to be effective when it is provided by school teachers, a structural implementation of the program in the school curriculum will enhance the quality of the lives of adolescents and their families and will reduce costs in health care. In addition, the results of the study advances current knowledge on the underlying mechanisms of the development of depression and may aid the improvement of depression prevention programs in general.

**Trial registration:**

Dutch Trial Register NTR3110

## Background

Research pointing to the importance of cognitive distortions in the etiology and maintenance of depressive feelings has led to the development of cognitive behavioral interventions for youth. These interventions are not only used for the treatment of existing disorders, but also for the prevention of new cases. Recent meta-analyses suggest that preventive interventions can significantly reduce depressive symptoms or risk for future depressive symptoms compared to control groups [1-3]. More research is needed to test if depression prevention programs are effective when implemented in community settings under real-world conditions, and to uncover the causal mechanisms and potential mediators of the effects [1].

One of the best studied depression prevention programs is the Penn Resiliency Program (PRP) [4]. PRP is a theory-based universal school-based depression prevention program designed for early adolescents (ages 10-14 years) that teaches cognitive-behavioral and social problem-solving skills. Although PRP is described as not having replicated effects across trials in the meta-analytic review of Stice et al. [3], positive conclusions about this program are drawn in an evaluation of all of the 17 existing controlled studies evaluating PRP with 2,498 participants in total [1]. Researchers testing the Penn Resiliency Program often used rigorous experimental designs with extended follow-ups (up to 36 months) showing small but significant and consistent systematic effects on depressive symptoms, especially at 12-month follow-up assessments. Concluding, PRP seems to be a thoroughly studied theory-based program and a good basis for further development of depression prevention. In the Netherlands, no school-based depression prevention program for adolescents exists as of yet and therefore the PRP-program has been translated and rigorously adapted to the Dutch situation in close collaboration with the original developers. The Dutch program is titled "Op Volle Kracht" (OVK) [5]. The primary aim of the present study is to test the transportability and effectiveness of OVK when it is delivered by school teachers and provided to adolescents with a high risk to develop depressive symptoms (selective prevention).

Selective prevention implies focusing on a population whose risk is deemed to be above average to develop symptoms of a given disorder. This type of prevention has been found to be more effective than universal prevention [6,7]. Commonly distinguished groups with high risk for developing depressive symptoms are youth with: elevated depressive symptoms at baseline, a pessimistic explanatory style, parents with mood disorders, family conflicts, or youth who belong to an ethnic minority, live in low income areas and who are more exposed to life stressors [3,7-11]. Youth from families with a low social economic status are exposed to chronic levels of uncontrollable negative life events and to more maternal distress because of greater economic hardship [8]. Selective prevention is relevant for people in the teenage years [6], because depression rates begin to rise in early adolescence with a peak in mid-late adolescences [12]. In the present study, a selective prevention program for depression is targeted at adolescents living in low income areas in the Netherlands.

Since the purpose of the OVK program is to *prevent *youth from developing depression symptoms, a structural, easily accessible implementation on a large scale is needed to reach early adolescents who have not developed clinical depressive symptoms yet. This will be achieved by implementing the program in the regular school curriculum. No stigmatization will occur as a result of singling out individuals to receive the program. In addition, we expect the effects of the class-based program to be more easily consolidated because the classmates will interact and learn from each other in day-to-day experiences. For a feasible implementation of the program in the school curriculum, the following pragmatic and logistic arguments and costs have to be taken into account. Because hiring external professionals for providing the program is too expensive for most schools, it is important that school teachers are able to deliver the program. It is therefore pivotal to study if school teachers can provide the program as effectively as clinicians and/or the developers of the program, and to evaluate practical implementation challenges and difficulties. Meta-analyses of the PRP program show significant effect sizes regardless of group leader type [1], although it appears that effect sizes are higher when the program is delivered by professional interventionists compared to endogenous providers (e.g. teachers) [3,4,11].

### Mechanisms

In addition to studying the main effects of this program on symptoms of depression, the mechanisms and possible factors underlying the effects of the program are of great interest. To this end, the mediating effects of two specific concepts will be examined in the current study: distorted cognitions and alexithymia. Distorted cognitions are important determinants of depressive feelings. Three central theories explain the etiology and maintenance of depressive feelings with the role of cognitions: Beck's cognitive theory of depression [13], the hopelessness theory of depression [14] and the response styles theory [15]. According to Beck's theory, stressful events activate maladaptive self-schemata (i.e. a style of cognitive interpretation) which generates specific cognitive errors such as 'overgeneralization' and 'catastrophizing'. The hopelessness theory [14] states that an attributional style with negative outcome expectancy and expectations of helplessness about changing the likelihood of occurrence of these outcomes are causal for developing a (subtype of) depression. People with a negative attributional style have a tendency to attribute negative events to stable, global and internal factors which leads to hopelessness and consequently to symptoms of depression. Both theories describe a diathesis stress component [16]; the cognitive styles are only activated if they are accompanied by negative life events. The response styles theory [15] argues that the severity and duration of the symptoms of depression are determined by three styles in which individuals respond to their symptoms of depression: rumination (excessive thinking about the same topic), distraction and problem-solving. In research, the response style 'rumination' has been found to have moderating effects on the relation between life events and depressive symptoms; adolescents with a rumination response style are more likely to experience depressive symptoms when reporting more life events [17]. To study elevations in depressive symptoms as a consequence of cognitive distortions, longitudinal studies are needed so temporal sequences can be analyzed [18]. Research on cognitive distortions using longitudinal designs is however very limited [19]. We hypothesize that the OVK program will prospectively decrease the cognitive distortions of the adolescents and in turn will influence the reported depressive symptoms.

Another theoretical concept we expect to be highly relevant in relation to depression prevention programs is alexithymia. Alexithymia refers to difficulties in experiencing and verbalizing emotions and difficulties in emotional self-regulation [20]. An impaired emotion processing ability is suggested to lead to negative mood states and support for this hypothesis is found with cross-sectional data: children who score higher on alexithymia are found to ruminate and worry more about emotion-evoking situations compared to children who score lower on alexithymia [21]. Diminished alexithymia, in turn, is associated with a reduction of depressive symptoms, and although it is still unclear if cognitive behavioural therapy can reduce alexithymia, the first hopeful results are reported [22]. We hypothesize that the OVK program leads to less alexithymia and subsequent lower levels of depressive symptoms.

The first goal of the current study is to test if the OVK program prevents symptoms of depression when the program is delivered by teachers during school hours to a whole class of adolescents. The second goal is to study the mechanisms and possible factors underlying the effects of the program.

## Methods/Design

### Design

The present longitudinal study involves a randomized controlled trial (RCT) with two conditions (intervention versus control) (see Figure 1) in which the effectiveness and the underlying mechanisms of the Dutch school-based depression prevention program Op Volle Kracht will be examined among adolescents from low income areas. The adolescents in the classes that will be assigned to the intervention condition will receive the 16-week OVK program from their teacher. Adolescents in the control condition will receive the usual school curriculum. While alternative interventions to control for nonspecific intervention ingredients are included in some of the PRP studies [4], the approach of 'care as usual' is chosen in the present study because no other school-based depression prevention program is currently implemented in the Netherlands. Still, some schools do provide social skill programs and we did not forbid schools to conduct those programs. The extent to which participants are involved in other prevention programs during the course of the study will be registered.

**Figure 1 F1:**
[figure not shown]
**Study design**.

Assessments in both the intervention and control condition will be conducted through a 50-minute web-based self-report questionnaire during school hours that will be administered at baseline, post-intervention and at two follow-ups (at 6 and 12 months). Participants do not receive incentives for filling out questionnaires. A low attrition rate is expected, because the measurements are administered during the regular school hours. The teachers will be motivated to keep complying to the protocol through personal email contact with the research team in which they receive results about the assessments on school level.

### Participants and procedure

All the secondary schools in the Netherlands that meet the criterion of having at least 30% of their pupils inhabiting low income areas will be approached for participation in the study. In the Netherlands, this information can be obtained from the Dutch Ministry of Education, Culture and Science and it is based on the average income in the postal code area in which the pupils live. The eligible schools are predominantly situated in urban areas. Two other selection criteria are the educational level and age: pupils from vocational training up to pre-university level and from the 7^th ^and 8^th ^grade (range 11 to 14 years old) are selected. Two weeks after approaching the school by means of a written invitation, they will be contacted by telephone. If they are interested in participating in the study, a personal visitation will follow and classes will be selected. From the participating classes, none of the pupils will be excluded, to avoid stigmatization and social exclusion. With support from the schools, all parents will receive a letter to inform them about the content and aim of the program as well as the procedures of the study. Permission from the parents for their child's participation will be obtained through informed passive consent. If parents do not give permission for participation in the study, the adolescents will still attend the OVK program because it is taught in the regular school curriculum, but no data will be collected from them. To protect confidentiality of the data provided by the participating adolescents a unique code will be assigned to each participant. The Ethical Committee of the Faculty of Social Sciences at the Radboud University Nijmegen approved the study's protocol.

### Randomization

The classes will be randomly assigned to two conditions (intervention or control). An independent researcher will perform the allocation before the baseline assessment will be administered. Randomization will be carried out centrally on class-level and within schools to control for school characteristics, using a computerized random number generator with blocked randomization scheme (block size 2) and stratified by level of education (high versus low).

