### Sample size

Power analysis (G-power) was conducted based on a 12-month effect size of .20. Although the expected effect size for a depression prevention program for high-risk youth is .40 (based on research of [11]; see also [3], the formulated effect size is more conservative, because the intervention will be conducted in classes of approximately 25 adolescents per class instead of 10 to 15 adolescents per group - as is done in some other school-based prevention programs [1]. For the power analysis, we considered potential loss of power due to clustering of data in groups at schools and due to multiple imputation and testing of mediational mechanisms. A maximum of 20% attrition over time has been taken into account as well. The sample sizes need to be 662 students per condition (alpha < .05, power = .80) and therefore the total sample size at baseline was determined to include 1,324 participants.

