### Intervention

The OVK program will be taught by intensively trained school teachers and covers cognitive-behavioral and social problem-solving skills. Within 16 lessons of 50 minutes that are delivered during school hours, adolescents learn to detect inaccurate thoughts, to evaluate the accuracy of those thoughts, and to challenge them by considering alternative interpretations. They also learn techniques for assertiveness, negotiation, decision-making, social problem-solving and relaxation. The skills in the program can be applied to many contexts of life, including relationships with peers and family members as well as achievement in academics or other activities. Details about the content of the program are described extensively elsewhere [5]. To be able to deliver the program, the school teachers of the classes in the intervention condition will receive a 4-day training by two staff members of the research group; both of them are experienced and licensed psychologists and both are experts in cognitive behavioral therapy. The teachers receive a detailed manual of the program as guideline and they have the option to contact the trainers for additional support during program delivery.

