### Statistical analysis

Data will be analyzed in accordance with the intent-to-treat principle but will also be analyzed separately for the completers only. Multiple imputations will be used for missing observations at follow-ups. The hypotheses will be tested with regression analyses for dichotomous and linear outcome measures in MPLUS 5.1 [37]. We will check for possible baseline differences between the two conditions in demographic variables (e.g. age, sex, school level, and ethnic background) and depressive symptoms. Moreover, variables that show different distributions between the two groups will be entered as confounders in all models testing the effectiveness of the intervention. The cluster effect - students are 'nested' in classes - will be handled by getting robust variance-related estimates using procedures for design-based analyses, (cf. [38]). We will correct for the cluster effects at class-level, as the interventions will be carried out in classes. Reporting of the results of the study will be in accordance with the CONSORT statement [39]. Mediation models will be tested with procedures as suggested by MacKinnon et al. [40].

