### Strengths and limitations

One of the strengths of this study concerns the rigorous research design of a randomised controlled trial with a large sample (N = 1,324) to analyse the underlying mechanisms and the sequence of change in the parameters. Another strength is the assessment of the cognitive distortions as possible mediators of symptoms of depression, which are based on three well-established cognitive theories [13-15]. Further, the added construct alexithymia has not yet been studied thoroughly in combination with depressive symptoms in youth. In addition, other highly relevant outcomes, such as academic achievement, will be measured to evaluate if other effects besides stimulating mental health might be reached by this program. Further, all assessments will be completed during school hours, which will ensure low attrition rates. An additional strength of the study is that the program will be delivered by teachers in a school setting, because the results will be of great importance in the discussion about practical implementation under real-world conditions (see also [1]). Last, the schools that will be participating in the study have a high diversity in school characteristics, e.g. Christian, Islamic, which generates a good external validity for the results of the study.

On the other hand, several limitations of this study exist. First, probably primarily motivated schools will join in the study, which may limit generalizability of the results to all schools. Second, by using a within-school design (as opposed to a between-schools design), contamination effects between the experimental and the control group could occur, although we expect to minimize these effects by delivering the program to entire classes instead of parts of classes. Third, the measurements are solely based on self-reports. Nevertheless, with respect to internalizing problems, it has been shown that adolescents are probably better informants compared to their parents or teachers [42]. At last, no integrity check of the delivery of the program will be conducted because of financial restrictions. However, the teachers will report on program adherence by filling out forms through which they report which (part of the) lessons they have covered.

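### Classes are allocated before the baseline questionnaire with no stated step to withhold the arm, so the self-reported baseline CDI may depend on the arm and bias the adjusted effect

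*Protocol article*

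**What the plan says.** All references are to the protocol article.

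- **Order.** Randomization: "An independent researcher will perform the allocation before the baseline assessment will be administered".
- **Unit.** Same section: "Randomization will be carried out centrally on class-level and within schools to control for school characteristics". The scheme is computer-generated in blocks of two and stratified by education level.
- **Who must learn the arm.** Intervention: "the school teachers of the classes in the intervention condition will receive a 4-day training by two staff members of the research group". The training is not dated relative to baseline.
- **Consent.** Participants and procedure: "Permission from the parents for their child's participation will be obtained through informed passive consent". The letter goes to all parents. Its timing relative to allocation is not given. The section adds: "If parents do not give permission for participation in the study, the adolescents will still attend the OVK program". Refusal stops data collection only.
- **Measurement.** Strengths and limitations: "Third, the measurements are solely based on self-reports".
- **Use of baseline.** Statistical analysis has the arms compared at baseline on demographic variables and depressive symptoms, and then: "variables that show different distributions between the two groups will be entered as confounders in all models testing the effectiveness of the intervention".
- **Target effect.** Sample size: "Power analysis (G-power) was conducted based on a 12-month effect size of .20".

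The limitations listed in the Discussion include contamination between arms and reliance on self-report, but not the order of allocation and baseline.

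**The concern.** Central allocation by an independent researcher protects how classes are assigned. It does not control who knows the result afterwards. With allocation done first, the arm can be known in a school when pupils fill in the baseline questionnaire. Intervention teachers have to be told before they can be trained. With blocks of two inside a school and education level, knowing one class's arm can reveal that of its paired class.

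The pupil is the assessor of the CDI. A pupil who knows that the class will, or will not, receive a depression programme may answer differently. A baseline value that depends on the arm is not a safe covariate. The plan's rule makes this worse, because an arm-related shift raises the chance that baseline CDI looks imbalanced and enters every effectiveness model. Over-reporting in the intervention arm would exaggerate the benefit after adjustment, and under-reporting would hide it.

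**Working it through.** **Documents side by side.** Randomization fixes allocation before baseline. Intervention requires that some staff know the arm before lessons start. No section says that the arm is withheld until baseline is complete. Statistical analysis then lets baseline depressive symptoms decide their own entry as a covariate. The stated order therefore leaves the route open, although no section says that early disclosure occurs.

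**Inputs from the article.** Target effect 0.20 SD; 662 pupils per condition; about 25 per class. The article gives no figure for the bias itself, so there is none to reproduce.

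**Assumed inputs.** An arm-related shift *s* in baseline CDI of 0.02, 0.05 or 0.10 SD, confined to baseline, and a baseline-to-outcome slope *b* of 0.4 to 0.7.

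**1. Baseline CDI always adjusted for.** Bias = *s* × *b*. For a change score, which the article does not say it will use, bias = *s*.

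| *s* (SD) | *s* × *b* (SD) | % of 0.20 | Change score, % of 0.20 |
|---|---|---|---|
| 0.02 | 0.008 to 0.014 | 4 to 7 | 10 |
| 0.05 | 0.020 to 0.035 | 10 to 18 | 25 |
| 0.10 | 0.040 to 0.070 | 20 to 35 | 50 |

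**2. Baseline CDI adjusted for only when an imbalance is detected.** The article states no criterion, so a two-sided 5% test is assumed. Take *s* = 0.05 and *b* = 0.6, for which permanent adjustment gives 0.05 × 0.6 = 0.03 SD (15% of target).

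- Standard error of the baseline difference without clustering: √(2/662) = 0.055. The shift is *d* = 0.05/0.055 = 0.91 standard errors.
- Chance of being flagged: 1 − Φ(1.96 − 0.91) + Φ(−1.96 − 0.91) = 0.15.
- If flagged, the bias is *b* × *s*. If not, the true baseline difference *e* stays in the estimate. Its contribution is E[*e*; not flagged] = SE × [φ(1.96 + *d*) − φ(1.96 − *d*)] = 0.055 × (0.006 − 0.230) = −0.0123.
- Mean bias: 0.6 × (0.05 × 0.149 + 0.0123) = 0.012 SD, or 6% of target.
- With a design effect of 1.96 (1 + 24 × 0.04, intraclass correlation assumed), the standard error is 0.077, the chance of a flag is 0.10 and the mean bias is 0.010 SD, or 5% of target.

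At every other *s* and *b* in the table the same formula also gives less than permanent adjustment.

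**3. Differential opt-out, if the letter follows disclosure.** Shift in the arm contrast = difference in opt-out rates × difference in CDI between pupils who opt out and the rest. With assumed values of 3 to 8 percentage points and 0.25 to 0.5 SD, this runs from 0.03 × 0.25 = 0.0075 to 0.08 × 0.5 = 0.04 SD.

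**4. Unadjusted follow-up comparison.** A shift confined to baseline contributes nothing.

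**The case against.** The strongest reply is that performing an allocation is not the same as disclosing it. The list is drawn centrally by an independent researcher, the training is undated, and disclosure logistics are often left to a fuller protocol. A teacher's knowledge also does not prove that pupils know. This stands as a limit on the wording: early disclosure is an inference. It does not remove the point, because the order is a positive statement in the article and nothing in it offsets that order.

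A reader might infer more than the article supports in four ways:

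- **That parents know the arm when they opt out.** Participants and procedure does not place the letter after allocation. Consent is passive, whole classes take part, and refusal neither obtains nor avoids the programme. Differential opt-out is a secondary and probably small risk.
- **That the baseline CDI and the sample are contaminated.** The article supports a risk, not a fact. The size and direction of any shift are unknown.
- **That the treatment comparison is invalid.** Follow-up outcomes are still compared between randomised classes, and an unadjusted comparison is untouched by a shift confined to baseline.
- **That the bias is 15% of the target.** This is one assumed point, and it presumes that baseline CDI is always in the model. Under the stated rule a 0.05 SD shift would often go undetected, and the average bias falls to about 5% to 6%.

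**Conclusion.** The point holds as an avoidable design risk. Allocation precedes a self-reported baseline, no step withholding the arm is described, and the analysis rule can carry an arm-related baseline shift into the effect estimate. If baseline CDI is adjusted for, the illustrative bias is 0.008 to 0.07 SD, or 4% to 35% of the 0.20 target, and it is smaller on average if adjustment depends on a detected imbalance. These figures rest on an assumed shift and slope and on the arm being known before baseline, none of which the article gives. The stated sample size is not affected. The change is worth making because it is cheap, not because the trial fails without it.

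**What to change.** In Randomization, reverse the order: within each school, select classes, close the parental opt-out, complete baseline, then allocate. If the list must be drawn earlier, state that the independent researcher holds it and releases it to a school only after that school's baseline is complete. In Participants and procedure, state that the opt-out closes before allocation or its release.

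If baseline has already been collected, report opt-outs by arm and who knew the arm at baseline, pre-specify covariates instead of choosing them by observed imbalance, and add a sensitivity analysis without baseline CDI.

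The cost is timing. Training of intervention teachers has to follow baseline, which may delay the start of lessons. The article gives no dates, so the delay cannot be sized. No extra staff, data or participants are needed.
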